### Combination intervention package

At health facilities randomly assigned to CIP, the intervention was delivered to all TB/HIV patients during regular clinic visits as part of routine care. All nurses and VHW affiliated with the TB/HIV clinic were trained to implement the CIP. CIP contained programmatic, structural, and psychosocial components, including: 1) nurse training and mentorship in TB/HIV co-treatment, using a clinical algorithm; 2) reimbursement of transportation costs to monthly clinic visits for patients and treatment supporters; 3) health education for patients and treatment supporters by VHW using a treatment literacy curriculum; and 4) real-time adherence support using short message service (SMS) text messaging and trained VHW. Table 1 shows a comparison of the study arms.

**Table 1 T0001:** Comparison of study arms

	Standard of care (SOC)	Combination intervention package (CIP)
Training on national TB guidelines for nurses	X	X
ART provision to TB/HIV patients in integrated clinics	X	X
Patient-identified treatment supporter for TB treatment	X	X
Nurse training and mentorship in TB/HIV co-treatment using a clinical algorithm		X
Reimbursement of transportation costs to monthly clinic visits for patients and treatment supporters		X
Health education for patients and treatment supporters by village health workers using TB/HIV treatment literacy curriculum		X
Real-time adherence support using automated SMS text messages and trained village health workers		X

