### Primary and secondary endpoints

Primary outcomes include: 1) ART initiation, 2) ART retention, and 3) TB treatment success. Secondary outcomes include: 1) time to ART initiation, 2) ART adherence, 3) change in CD4+ count, 4) sputum smear conversion, 5) TB treatment adherence, 6) cost-effectiveness, and 7) acceptability. All outcomes pertain to the individual participant level. ART initiation is defined as the percentage of TB/HIV patients newly registered during the period of observation who initiated ART during TB treatment, based on review of clinic records. ART retention is defined as the percentage of measurement cohort participants who attended their 6-month clinic visit (within a 1-month window) and reported ART use. Deaths and transfers will be considered not retained. TB treatment success is defined as the percentage of TB/HIV patients whose TB treatment outcome is documented in the TB register or treatment card as treatment completion or cure, as defined by the WHO (40). Time to ART initiation will be expressed as the number of days from TB treatment initiation to ART initiation. Adherence is determined separately for ART and TB treatment and defined by the percentage of total prescribed doses ingested, averaged across medicines for each month of treatment, from the unannounced pill counts. Change in CD4+ count is defined as the difference in CD4+ count 6 months after TB treatment initiation. Sputum smear conversion is defined as the percentage of smear positive pulmonary TB cases that converted to smear negative after 8 weeks of treatment (40). Incremental cost-effectiveness will be estimated as the ratio of the incremental costs of the CIP per ART initiation, retention, and TB treatment success. Acceptability of intervention components will be characterized via in-depth qualitative analysis and interpretation (41). Table 2 lists the study outcomes for each group of participants.

**Table 2 T0002:** Study outcomes

Study outcome	All TB/HIV patients	Measurement cohort	Key informants – ART early initiators	Key informants – ART non/late initiators	Key informants-health care workers
ART initiation^a^	X				
ART retention^a^		X			
TB treatment success^a^	X				
Time to ART initiation	X				
ART adherence		X			
Change in CD4+ count		X			
TB treatment adherence		X			
Sputum smear conversion	X				
Incremental cost-effectiveness		X			
Acceptability of intervention components			X	X	X
Reasons for ART non/late initiation				X	

a Primary outcomes.

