### Sample size and power calculations

Power calculations for all TB/HIV patients were based on our primary outcomes ART initiation and TB treatment success. Based on previous programmatic data, we anticipated an average of 100 newly registered TB/HIV patients at each of the 12 study clinics over the first 24 months of observation. When the study was designed, available data demonstrated that only 27% of HIV-infected TB patients in Lesotho had received ART, and the TB treatment success rate was 70% for new smear positive cases, 64% for new smear negative and extrapulmonary cases, and 62% for retreatment cases (HIV-positive and HIV-negative cases combined) (42). Assuming a two-sided Farrington & Manning Likelihood Score Test with *α*=0.05 and an intra-cluster correlation coefficient (ICC) of 0.05, we will have 83% power to detect a difference in ART initiation from 40% (SOC) to 60% (CIP), and 91% power to detect a difference in TB treatment success from 65% (SOC) to 85% (CIP) (PASS 2008, NCSS Statistic Software). As per standard practice, patients who die or are lost to follow-up before ART initiation or TB treatment completion are considered to have not initiated ART or to have not achieved TB treatment success, respectively, and thus power calculations for these outcomes do not include an allowance for attrition.

Power calculations for measurement cohort participants were based on our primary outcome ART retention. Assuming 100 TB/HIV patients in each of the 12 study clinics, 40% ART initiation at SOC clinics, and at least 80% study enrollment, we aimed to enroll 384 participants (32 per clinic) initiating ART in the measurement cohort. Assuming a two-sided Farrington & Manning Likelihood Score Test with *α*=0.05 and ICC of 0.05, we will have 87% power to detect a difference in ART retention from 70% (SOC) to 90% (CIP).

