### Data analysis

An intent-to-treat analysis will be used. In addition, when measuring adherence in the measurement cohort, an as-treated analysis will be used to exclude participants who died or discontinued medications due to adverse events. Generalized linear mixed models (Proc Glimmix procedures in SAS v9.3 with a random intercept for study site) will be applied to test for a difference between study arms for dichotomous (ART initiation, ART retention, TB treatment success, sputum smear conversion) and continuous (ART adherence, change in CD4+ count, TB treatment adherence) outcomes; frailty models (Proc Phreg procedures in SAS v9.3 with random intercept for study site) will be utilized for time to event analysis (time to ART initiation) to account for the clustering of characteristics that may occur among patients attending the same study site. These approaches will provide appropriate adjustments to the standard errors accounting for potential non-independence of observations (43). Models will include fixed effects for study condition, patient characteristics, time-varying adherence measures and CD4+ count (for change in CD4+ count) and random effects for site. Participants who transferred to another site before ART initiation will be censored, and death before ART initiation will be treated as a competing risk.

For the cost-effectiveness analysis, a model will be created to estimate the incremental cost of CIP relative to SOC. The costs will be composed primarily of the variable costs involved in training nurses and convening VHW, but will also include the costs of administering SMS messages and the fixed costs involved in administering the intervention. The incremental cost-effectiveness of CIP will be estimated as the ratio of the incremental costs to incremental effectiveness with effectiveness measured in terms of the study's primary outcomes.

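### The model comparing arms on change in CD4+ count adjusts for adherence, which the intervention targets, so its arm coefficient is not the total effect of assignment

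*Protocol article*

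**What the plan says.** All of the following is in the protocol article.

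- **Purpose of the models.** Under Data analysis, generalized linear mixed models "will be applied to test for a difference between study arms"; change in CD4+ count is one of the continuous outcomes listed there.
- **Covariates.** The same section states: "Models will include fixed effects for study condition, patient characteristics, time-varying adherence measures and CD4+ count (for change in CD4+ count". The sentence then closes the parenthesis and adds random effects for site.
- **Analysis principle.** The section opens with "An intent-to-treat analysis will be used".
- **The outcome.** Under Primary and secondary endpoints: "Change in CD4+ count is defined as the difference in CD4+ count 6 months after TB treatment initiation". The earlier value is not named.
- **Adherence as an outcome.** The same section lists "Secondary outcomes include: 1) time to ART initiation, 2) ART adherence, 3) change in CD4+ count", with TB treatment adherence further down the list. Adherence is the percentage of prescribed doses taken, "averaged across medicines for each month of treatment, from the unannounced pill counts".
- **Adherence as a target.** Under Combination intervention package, the fourth component is "real-time adherence support using short message service (SMS) text messaging and trained VHW". The sections on the programmatic and psychosocial components add nurse adherence messages, counselling referrals and weekly contact from village health workers.

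The article gives no arm comparison for CD4+ change without adherence, and it does not call the adjusted model exploratory or a mediation analysis.

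**The concern.** A covariate in a model that compares randomised arms should not be something the allocation can change. Adherence is observed after allocation, the CIP is built to raise it, and it is a plausible route to CD4+ recovery. With adherence held fixed, the coefficient for study condition answers a narrower question: how CD4+ change differs between arms among patients with the same adherence. That is a residual effect. It has a causal meaning only if nothing unmeasured drives both adherence and CD4+ recovery, and randomisation does not secure that condition.

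The practical risk is a misread result. If the CIP raises CD4+ mainly by improving adherence, this model could show little or no arm difference even though the package worked as designed.

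The CD4+ covariate raises a second, smaller question. The words describing adherence as time-varying may or may not extend to it, and the two readings have very different consequences.

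**Working it through.** **1. Does adherence enter the CD4+ model on every reading?** The parenthesis can qualify CD4+ count alone or both covariates.

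- If it qualifies both, adherence is in the CD4+ change model only.
- If it qualifies CD4+ count alone, adherence is in the models generally, including the one for CD4+ change.

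Either way the CD4+ change model contains adherence. On the second reading it could also enter other outcome models, but only where adherence is observed. Pill counts and adherence questionnaires belong to the measurement cohort (Data collection; Table 2), so ART initiation, TB treatment success, time to ART initiation and smear conversion are out of reach. Among the primary outcomes, only ART retention could be affected.

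**2. What does the adjusted coefficient estimate?** Let T be the total effect of assignment on CD4+ change, a the effect of assignment on adherence, b the effect of adherence on CD4+ change, and d the remaining effect.

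- Linear mediation: T = d + a·b.
- Mediated share: q = a·b / T.
- Coefficient with adherence in the model and no confounding: d = T × (1 − q).

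**3. Numbers.** The article states no effect size, SD or power for CD4+ change, so there is no plan figure to reproduce. For illustration, the cohort layout comes from the article: "we aimed to enroll 384 participants (32 per clinic) initiating ART in the measurement cohort" (100 × 0.40 × 0.80 = 32; 32 × 12 = 384), with its ICC of 0.05. The rest is assumed: T = 30 cells, SD 120, and an adherence shift a of 0.5 SD. Each row rests on 4,000 simulated trials per scenario, using least-squares arm coefficients.

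The last two columns add an assumed unmeasured factor that loads 0.5 on adherence (variance 1) and raises CD4+ change by 0.5 × 120 × 0.5 = 30 cells per SD. It inflates the adherence slope by 0.5 × 30 = 15 and moves the arm coefficient by −0.5 × 15 = −7.5.

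| Share q | 30 × (1 − q) | Simulated, baseline CD4+ only | Simulated, plus adherence | 30 × (1 − q) − 7.5 | Simulated, plus adherence, with confounder |
|---|---|---|---|---|---|
| 0% | 30 | 29.4 | 29.5 | 22.5 | 23.2 |
| 25% | 22.5 | 29.6 | 22.1 | 15 | 15.2 |
| 50% | 15 | 29.9 | 15.1 | 7.5 | 6.9 |
| 75% | 7.5 | 29.7 | 7.3 | 0 | −0.2 |
| 100% | 0 | 29.4 | −0.6 | −7.5 | −7.5 |

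Without adherence, with or without baseline CD4+ and with or without the confounder, the estimate stays between 29.4 and 30.8. With adherence it falls by the mediated share, and confounding can bias it even when nothing is mediated. A factor acting on adherence and CD4+ in opposite directions would reverse the sign of the 7.5, so the direction of the confounding bias is not fixed.

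**4. The CD4+ covariate.** Assume a baseline SD of 100, a change SD of 120 and T = 30.

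- **Baseline value:** the arm coefficient is unchanged, at about 30.
- **6-month value alone:** the slope on that value is 120² / (100² + 120²) = 14,400 / 24,400 = 0.59, so the arm coefficient is 30 × (1 − 0.59) = 12.3 (simulated 12.2).
- **Both values:** change is the difference of the two covariates, so the arm coefficient is exactly 0.

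**The case against.** The strongest reply is that this is one of seven secondary outcomes, in the measurement cohort only and with no power calculation, described in a condensed article whose analysis plan may say more. The points about rank and power stand and limit the severity. The last does not dispose of the matter, because the sentence does not leave the covariates open: it names adherence as one of them.

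Several stronger readings are tempting, but the documents do not support them.

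- **That the model conditions on the outcome itself through a time-varying CD4+ count.** The wording allows this but does not say it. For a single change at 6 months, the natural covariate is baseline CD4+, which does no harm. Only an ambiguity is established.
- **That the plan contradicts its intent-to-treat statement.** In that section, intent-to-treat is set against an as-treated analysis that excludes some participants, so it concerns who is analysed. Adding a mediator excludes and reassigns nobody. It changes what is estimated.
- **That adherence contaminates the analyses generally.** It is not observed for the all-patient outcomes.
- **That patients without pill counts would be dropped.** The article does not say how adherence is summarised in this model or how missing months are handled.

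It is also fair to say that removing adherence would not make this a fully randomised comparison, since the cohort consists of consenting patients who started ART within 2 months of TB treatment. That is a separate limitation and no reason to add a second one.

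**Conclusion.** The point holds for adherence. As written, the arm coefficient for change in CD4+ count is not the total effect of assignment in the cohort. It omits whatever acts through adherence and is exposed to adherence–CD4+ confounding. This follows from the stated covariates and the described intervention, and needs no numerical assumption.

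The size cannot be derived from the documents. Proportional shrinkage by the mediated share holds under linear mediation without confounding. The figures of 30 cells, SD 120 and the chosen shares are illustrations, so a particular percentage loss should not be read as a finding. On the CD4+ covariate, the conclusion is only that the article must say which value is meant.

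This is a should-fix matter. On the narrower reading of the parenthesis no primary outcome is touched. On the wider one, ART retention is the only primary outcome that could be.

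**What to change.** - Make the arm comparison for change in CD4+ count a mixed model with study condition, facility-type stratum, CD4+ count named as the baseline value, baseline patient characteristics and a random effect for site.
- Move the model with time-varying adherence to a separate analysis labelled exploratory or mediation, and state there that it assumes no unmeasured common causes of adherence and CD4+.
- State that adherence does not enter any other arm comparison in the measurement cohort, such as ART retention.

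The cost is a change of wording in the analysis section. No new data are needed: a change in CD4+ already requires an earlier value, and the adherence data remain in use for the exploratory model.

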### Study setting

The study was conducted in Berea District of the Kingdom of Lesotho, a lower middle income sub-Saharan African country of 2.1 million people (27). In 2014, 9,856 cases of all forms of TB were reported. The treatment success rate for new and relapse TB cases registered in 2013 was 70%, short of the WHO's 85% target (1).

The majority of people in Lesotho receive health care at health centers staffed by nurses, who provide outpatient care and preventive services. Complicated cases are referred to district hospitals. Nurses can initiate TB treatment for smear positive cases at the health center level; smear negative cases are referred to the hospital for evaluation and treatment initiation by a medical officer. At the health center level, TB/HIV services including provider-initiated HIV testing and counseling and the provision of cotrimoxazole prophylaxis and ART are well integrated with TB treatment and are provided as one-stop services. At the hospital level, ART is integrated within TB clinics, as per national guidelines. Typically, each clinic providing TB/HIV services is staffed by one to three nurses, plus one or two lay counselors, supported by 20–30 village health workers (VHW). TB treatment, ART, and cotrimoxazole are dispensed on-site. Sputum smear microscopy is available through specimen transport to district hospitals by motorbike on a weekly basis.

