### Facility selection

Twelve of 17 public health facilities in Berea District were selected for participation. The remaining five health facilities were excluded from the sampling frame because patient volume was very low (on average, fewer than six TB patients notified per quarter). Both hospitals (*N*=2) and health centers (*N*=10) were included to enhance generalizability. A single district was chosen in collaboration with MOH to enhance internal validity by ensuring comparability of health facilities randomized to either study arm, and maximize cost efficiency.

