### Assignment to study arm

Assignment to a study arm was done at the health facility level as opposed to the individual participant level. Health facilities were stratified by facility type (i.e. hospital or health center), and then numbered sequentially within each stratum. Intervention status was randomly assigned within each stratum by an investigator using SAS v. 9.3 (SAS Institute, Cary, NC). All HIV-infected TB patients at facilities assigned to the SOC condition received standard of care supported by the Lesotho MOH, while all those enrolled in facilities assigned to the CIP condition received the standard of care plus the intervention package. Given the nature of the interventions, participants, health care workers, and study staff were not blinded to the assigned study arm.

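### Facilities were randomised within hospital and health-centre strata, but the listed model terms omit facility type, so precision is lost if the two strata differ materially

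*Protocol article*

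**What the plan says.** Under Assignment to study arm, the article says: "Health facilities were stratified by facility type (i.e. hospital or health center), and then numbered sequentially within each stratum". It continues: "Intervention status was randomly assigned within each stratum by an investigator". Facility selection gives the stratum sizes: "Both hospitals (*N*=2) and health centers (*N*=10) were included to enhance generalizability". The ratio of arms within each stratum is not stated.

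Under Data analysis, the dichotomous and continuous outcomes are to be fitted with "Proc Glimmix procedures in SAS v9.3 with a random intercept for study site", and time to ART initiation with a frailty model that has the same random term. The model content is then listed: "Models will include fixed effects for study condition, patient characteristics". The rest of the list consists of adherence and CD4+ terms for the CD4+ outcome and a random site effect. Facility type is not in that list, and no other section adds it. It is a property of the site, so the reference to patient characteristics does not cover it.

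Study setting gives a reason why the strata might differ. Complicated cases go to district hospitals, and "smear negative cases are referred to the hospital for evaluation and treatment initiation by a medical officer".

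**The concern.** Stratified randomisation balances the stratum difference across arms, so that difference should not contribute to the uncertainty of the treatment effect. The model must be told this. With only a random intercept for site, a systematic difference between hospitals and health centres looks like ordinary site-to-site variation. The estimated between-site variance rises, the standard error of the arm effect rises with it, and the test becomes conservative. The trial has 12 clusters and at most 10 between-site degrees of freedom, so it has little precision to give away.

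**Working it through.** **Inputs from the article** (Sample size and power calculations): 12 clinics, 100 patients each (32 each in the measurement cohort), ICC 0.05, two-sided alpha 0.05. The effects are 40% vs 60% (ART initiation), 65% vs 85% (TB treatment success) and 70% vs 90% (ART retention). Stated powers are 83%, 91% and 87%.

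**Assumptions, not in the article:** 1+1 hospitals and 5+5 health centres by arm; equal cluster sizes; a linear analysis of site proportions in place of the planned mixed model; a hospital/health-centre gap d of 0 to 20 points.

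**1. The plan's own power.** The design effect is 1 + 99 × 0.05 = 5.95, so effective n per arm is 600/5.95 = 100.8. For the cohort it is 1 + 31 × 0.05 = 2.55, giving 192/2.55 = 75.3. The pooled normal formula then gives 81.6%, 91.3% and 87.4% (82.6% unpooled for ART initiation). The stated figures reproduce within 2 points. With t on 10 degrees of freedom they would be about 74%, 86% and 81%.

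**2. Effect of omitting facility type.** The variance of a site proportion within stratum is v = p(1−p) × (0.05 + 0.95/m), with p(1−p) averaged over arms:
- ART initiation: 0.24 × 0.0595 = 0.01428
- TB treatment success: 0.1775 × 0.0595 = 0.01056
- ART retention: 0.15 × (0.05 + 0.95/32) = 0.01195

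With one hospital among six sites, a gap d adds a sum of squares of 5d²/6 per arm on 5 degrees of freedom, that is d²/6, to the estimated variance. The ratio of interval widths, without versus with the term, is √(1 + d²/(6v)) × t(10)/t(9), where t(10)/t(9) = 2.228/2.262 = 0.985.
- d = 0: ratio 0.985, so adding the term widens the interval by about 1.5%.
- Break-even: 5.1, 4.4 and 4.7 points for the three outcomes.
- d = 10 points: 0.01/6 = 0.00167; ratios 1.04, 1.06 and 1.05.
- d = 20 points: 0.04/6 = 0.00667; ratios 1.19, 1.26 and 1.23.

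A beta-binomial simulation (40,000 runs per setting) gave 0.987 for all three outcomes at d = 0. It gave 1.04, 1.08 and 1.07 at 10 points, and 1.20, 1.30 and 1.28 at 20 points.

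**3. Direction.** In the same simulation of ART initiation without the term, type I error was 5.2% with no gap, 4.1% at 10 points and 1.9% at 20 points. Coverage was 94.7%, 96.0% and 97.8%.

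**4. Power with the total ICC held at 0.05.** Take p(1−p) = 0.25, so total site-mean variance is 0.05 × 0.25 + 0.24/100 = 0.0149. A 10-point gap accounts for d² × (1/6)(5/6) = 0.0014 of it, leaving 0.0135 within strata. The true standard error is then √(0.0135/3) = 0.067. For a 20-point effect, non-central t power is about 73% without the term (10 df) and 76% with it (9 df). With no gap, power without the term is also about 73%.

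**5. The only documented case-mix difference.** The article gives TB treatment success of 70% for new smear-positive cases and 64% for new smear-negative and extrapulmonary cases. Suppose hospitals held only the latter and health centres only the former. Then d = 6 points, d²/6 = 0.0006, and the ratio for TB treatment success is √(1 + 0.0006/0.01056) × 0.985 = 1.01.

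**The case against.** The best defence is that a journal article gives a condensed list. It names no individual covariate for the primary outcomes, does not say facility type is excluded, and the full analysis plan may include it. That possibility stands. It does not remove the mismatch: the article states the stratified design and also lists model terms down to the random site effect, and the two do not fit together.

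Three further points stand and limit the size:
- No hospital versus health-centre gap is given for any outcome, and the only related figures (70% vs 64%) lie close to break-even.
- If smear status or TB type is among the patient characteristics, part of the difference is already adjusted for.
- The article does not say where referred smear-negative patients are later registered or followed, so referral alone does not establish a large gap.

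A reader might infer that power for ART initiation falls to about 58% at a 20-point gap. That figure comes from adding the gap on top of a within-stratum ICC of 0.05. The article states one ICC of 0.05 for the clinics without reference to strata. Read as the total, it already includes any stratum difference, and power without the term does not fall.

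**Conclusion.** The point holds as a mismatch between the randomisation and the listed model, with a conservative and conditional consequence. It rests on the assumed 1+1 and 5+5 allocation, equal cluster sizes and a linear cluster-level stand-in for the mixed model. On that basis, omitting facility type is negligible or slightly favourable below a gap of about 5 points. It costs about 4% to 8% of interval width at 10 points and more only for larger gaps, before any recovery through patient covariates. Against the planned ICC it is a forgone gain, about 73% versus 76% power for ART initiation at 10 points.

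Three stronger readings are not supported. The article does not show that the intervals are too wide, because that depends on an unreported gap. Type I error is not inflated. The stated powers of 83%, 91% and 87% are not in error on this account.

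**What to change.** Add facility type (hospital or health centre) as a fixed effect in every generalised linear mixed model, and as a fixed effect or stratum in the frailty model for time to ART initiation. Reduce the between-site degrees of freedom from 10 to 9. State the within-stratum allocation in the same place.

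This is one term in each model statement and changes nothing in trial conduct. Because the factor comes from the randomisation, adding it is not a data-driven choice. The cost is one degree of freedom, about 1.5% wider intervals if the strata do not differ. The facility-type effect itself would rest on only two hospitals and should be treated as a design adjustment, not as a result to interpret.
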